### Blinding and randomization

Each participant will be randomized following screening and enrollment in the study. Participants will be randomized to either the immediate start (AEP) or delayed-start group (SP + AEP) using a computer-generated randomization sequence with block sizes of 10. Allocation details are kept in opaque envelopes and revealed sequentially. Due to the nature of the intervention only the data analyst will be blinded.

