#### Sleep parameters

Wrist worn actigraphy (MotionWatch 8© [MW8]; CamNTech) will be used to monitor sleep parameters, such as duration and sleep onset latency, pre and post intervention. Sleep diaries will also be collected. It has been suggested that actigraphy assessment is a useful supplement to self-report measures of sleep following TBI [51]. The MW8 has previously been used for sleep analysis in individuals with bipolar disorder [52] and stroke [53]. In older adults, subjective sleep quality has been found to differ from objective measures, such as actigraphy, supporting a best practice of using both measures [54].

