#### Blood biomarkers

Blood biomarkers of exercise and recovery will be evaluated to probe underlying mechanisms of response to AEP and SP. Blood samples (7 mL total) will be collected under clean technique from inner elbow at baseline, 6-weeks and 12-weeks of intervention. Markers of overall brain health and response to exercise, specifically brain-derived neurotropic factor, will be analyzed according to validated methods provided by Meso Scale Discovery (SD; Gaithersburd, MD, USA) on their electrochemiluminescence platform. Cytokines will be evaluated to further understand whether there is a chronic inflammatory response to injury in this cohort and whether that is affected by the intervention. Cytokine concentrations will be determined using the Bio-Plex Pro™ Cytokine, Chemokine, and Growth Factor Assays from Bio-Rad (Herkules, CA, USA). Samples will be assayed as instructed by the manufacturer. The plates will be read on a Luminex 200 apparatus (Applied Cytometry Systems, UK). Samples will be acquired and analysed using BioPlex Manager 6.0. Should there be a coefficient of variance of 20% or higher between two replicates, data points will be considered missing. Telomere lengths (TL) will be evaluated as they are known to be neuroprotective and resiliency promoting. In a rodent model, TL has been shown to decrease following mTBI [55]. DNA will be isolated from the red blood cell clot for telomere analysis. TL measurement using qRT-PCR will follow the protocol established by Cawthon [56].

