### Data management

Participants will be assigned a study ID number at the time of randomization by which they will be identified within the research team. Study data will be entered into a highly secure electronic REDCap database which requires double password protection to enter. Only research team members will have access to this database. Participant information or other data transmitted through USB will be encrypted. USB transfer of information will only be used when absolutely necessary and will be password protected. Paper copies of any data or participant information will be kept in a locked cabinet in a locked room in a locked university building.

All identifying information will be removed once all study participant numbers have been assigned and all data is collected. When data is downloaded for analysis, manuscript writing or abstract preparation all identifying information will be excluded. This information will be downloaded to a password protected SPSS file for analysis. No identifiable information will be retained once data collection is complete. All data will be retained for five years following project completion in accordance with Health Canada retention guidelines.

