### Analysis

The primary clinical outcome is the RPQ at 6-weeks of intervention. For the clinical outcome measures, two separate analyses will be run:
Outcome measures will be analyzed using two-way mixed ANOVA at baseline and 6-week timepoints. Two-way mixed ANOVA allows for analysis of group by time interaction effect. If a statistically significant group by time interaction effect is detected, indicating that group effect varies with time, or time effect varies with the group, simple effect testing will be used to analyze group effect broken down by time or time effect broken down by group. Should there be missing values, generalized estimating equation analysis will be employed.Outcome measures between groups (delayed-start vs. immediate start) following the aerobic exercise intervention only will be analyzed using two-way mixed ANOVA at the three primary timepoints: baseline, 6-weeks and 12-weeks.

The HERMES MRS data will be analysed to quantify GABA and glutathione levels using Gannet3, a spectral analysis tool. The PRESS MRS data will be analyzed to quantify NAA, glutamate, creatine and choline. Metabolite levels will be compared using an ANOVA model comparing groups at each of the three timepoints (as above). Additional exploratory analyses will investigate the correlations between metabolite levels and symptom burden. Whole brain ASL data will be processed to provide quantitative maps of tissue perfusion (cerebral blood flow) and group data will be compared on a whole brain basis. If no differences are detected, regional analyses may be applied. Resting state fMRI data will investigate differences in functional connectivity between groups and time points using both independent component analysis and seed-based approaches.

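### The reason given for blinding only the data analyst does not reach staff who assay blood, process MR data or score actigraphy; the protocol should say whether they work on coded material and who the analyst is (minor)

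*Protocol article*

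**What the plan says.** The Blinding and randomization section sets the rule and its reason in one sentence: "Due to the nature of the intervention only the data analyst will be blinded". No other section says that laboratory, imaging or actigraphy staff are masked.

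Other sections bear on how the objective measures become values:

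- **Data management:** "Participants will be assigned a study ID number at the time of randomization by which they will be identified within the research team". Whether the ID travels with or without the arm is not stated.
- **Blood biomarkers:** for the cytokines, "The plates will be read on a Luminex 200 apparatus", and "Should there be a coefficient of variance of 20% or higher between two replicates, data points will be considered missing".
- **Sleep parameters:** the wrist device "will be used to monitor sleep parameters, such as duration and sleep onset latency, pre and post intervention", with sleep diaries collected as well. No scorer or scoring rule is described.
- **Analysis:** "The HERMES MRS data will be analysed to quantify GABA and glutathione levels using Gannet3, a spectral analysis tool". Quantification of the PRESS spectra, perfusion processing and resting-state connectivity are described under the same heading. For perfusion, the group comparison is whole-brain first: "If no differences are detected, regional analyses may be applied".
- **Analysis, primary outcome:** "The primary clinical outcome is the RPQ at 6-weeks of intervention".

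**The concern.** A blinding rule should go as far as its reason allows. The nature of the intervention explains why a participant knows whether they are stretching or doing aerobic exercise, and why the staff who demonstrate stretches or update heart-rate prescriptions know it too. It does not explain why someone running a plate, fitting a spectrum or setting a sleep window should know it. The word *only* nevertheless leaves everyone except the analyst outside the blind.

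At stake is the quality of the secondary endpoints that do not rest on self-report: BDNF, cytokines, telomere length, brain metabolites, perfusion, functional connectivity and actigraphic sleep. If arm is known while a value is being accepted, rejected or scored, a reader cannot rule out that the choice leaned one way. Participants and coaches are unavoidably unblinded in this trial, so it is worth keeping these measures clear of a second, avoidable source of doubt.

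**Working it through.** The plan gives no figure on this point to reproduce, so the check sets the sections side by side and asks three questions of each group of endpoints.

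| Endpoint group | Does the stated reason require the handler to know the arm? | What the article fixes | What is left open |
|---|---|---|---|
| Cytokines | No | Manufacturer's instructions, machine-read plates, replicate variation of 20% or more set to missing | Little beyond handling and re-runs |
| BDNF, telomere length | No | Named platform for BDNF; an established PCR protocol for telomeres | Whether the 20% rule, which sits in the cytokine description, applies here too |
| GABA, glutathione, glutamate, NAA | No, for off-line processing | Software quantification named for HERMES | Who runs it, and how a poor spectrum is rejected |
| Perfusion, connectivity | No, for off-line processing | Whole-brain comparison first for perfusion | Who processes the images; any quality check |
| Actigraphic sleep | No | Device and diaries | Who scores, and how sleep windows are set |

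**Step 1: does the reason support the rule?** The second column is *no* throughout. The reason justifies leaving participants and intervention staff unblinded. It does not justify leaving these handlers unblinded.

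**Step 2: does another section mask them?** Data management comes closest. Identification by study ID is consistent with masked handling but does not establish it, because an ID can be used by someone who also knows the allocation.

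**Step 3: could the analyst already be the handler?** For MR data, yes. Quantification, perfusion mapping and connectivity all stand under Analysis, so the blinded analyst may be the person who does them. On that reading the MR rows are already met. It would not naturally cover blood assays, which are described in a different section, or actigraphy, for which no one is named. The optional regional perfusion step depends on a group comparison already made, so it belongs to the analyst rather than to upstream processing.

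**Step 4: how much is exposed?** With 56 participants and the three time points in the Measures section, there are 56 × 3 = 168 participant-visits if nobody drops out. That counts the material handled. It does not measure bias, and the document gives nothing from which bias could be calculated.

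**The case against.** The strongest reply has four parts.

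1. **The analyst may cover the MR work.** This stands as a real ambiguity and is why the point is conditional. It also shows why the term needs defining.
2. **The measures are largely mechanical.** Cytokine plates are machine-read and the replicate rule is fixed in advance, so dropping a discordant cytokine replicate is not left to taste. HERMES spectra are quantified by software. This stands, and it lowers the risk most for cytokines. A reader might infer that every objective endpoint is wide open to reader bias. The article does not support that: it describes no manual actigraphy scoring and no image quality-control step, so discretion there is inferred from the methods.
3. **A condensed article leaves tube labelling and operating procedures to the full protocol.** That is right for the detail, and nothing in the article says that laboratory or imaging staff are given the allocation. It does not dispose of the point, because the article states a positive rule that excludes them rather than staying silent.
4. **Full masking is not free.** Blinding whoever positions the spectroscopy voxels, with an unblinded participant in the scanner, would be more than relabelling. This stands, and voxel placement is not part of the request. Coded handling also has a small cost in labelling and task separation.

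The treadmill test lies outside this point. It depends on the participant's own ratings and effort under live supervision, and coding files would not protect it.

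**Conclusion.** The sentence limits blinding more tightly than its reason warrants. Unless the data analyst is intended to include those who assay, process and score, the secondary blood, MR and actigraphy endpoints are avoidably exposed to some bias through whatever discretionary steps exist. The magnitude cannot be derived, and it is likely smaller for cytokines than for measures with no stated acceptance rule.

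This rests on two assumptions: that the sentence means what *only* says, and that at least some processing steps involve judgement, which the article mostly does not describe.

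Two stronger conclusions might be drawn and are not supported. One is that the primary result is at risk from this: the primary outcome is a questionnaire completed by unblinded participants, and neither the flaw nor the remedy reaches it. The other is that the trial relies on these endpoints to confirm a symptom difference: the objectives give biomarkers and imaging a mechanistic role, and the metabolite-symptom correlations are labelled exploratory.

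Severity: minor. It is worth making because the change is cheap.

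**What to change.** Replace the sentence in Blinding and randomization with wording to this effect:

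> *Participants and staff who deliver the intervention are not blinded. The data analyst, and all staff who assay blood, process or quality-check MR data off-line, or score actigraphy, work on samples and files identified by study ID without arm. Exclusions are fixed before unblinding.*

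Add one line saying who the data analyst is and whether that role includes MR processing. No blinding of voxel placement at the scanner is asked for.

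**Cost:** coded labelling of tubes, scans and recordings using the study IDs already in place. Staff who also coach participants must process only coded files or exchange that task with a colleague. No additional staff, visit or procedure is needed, and the sample size is unchanged.

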### Interventions

#### Treatment arms

Once screening is complete and a participant is enrolled, they will be randomized to either begin the aerobic exercise protocol immediately (AEP, *n* = 28), or begin the aerobic exercise following a precursor placebo-like stretching protocol (SP, n = 28). Participants in both groups will complete a digital daily exercise diary for the duration of the protocol.

#### Aerobic exercise intervention

Participants are asked to complete approximately 30 mins of aerobic exercise, 5x/week for 12-weeks. The assigned exercise prescription will be 70–80% of max HR as achieved during exercise testing. Exercise prescriptions will be updated every 3-weeks. HR will be monitored by participants during exercise using a PolarH10 (Polar Canada) HR monitor, which connects to the *Polar Beat: Run & Fitness* app, allowing for ease of monitoring. Exercise location and mode of exercise (treadmill, outdoor walking or jogging, stationary bike, swimming or elliptical) will be at the discretion of participants and vary depending on exercise prescription and access. Mode and location of exercise will be discussed with a member of the study team at the initial and follow-up assessments and ability to continue will be assessed.

Exercise prescriptions will be based on HR at point of symptom exacerbation as determined using the Buffalo Concussion Treadmill Test (BCTT). The BCTT is an incremental treadmill exercise test following a modified Balke protocol [30], as first described by Leddy and colleagues, which progresses to the first sign of symptom exacerbation. All exercise testing will be under the supervision of a certified exercise physiologist. During all assessments a physician will be on call and will be paged in the unlikely event of an emergency. If there is a medical emergency requiring life supporting immediate medical attention 911 will be called. All members of the study team are first aid and CPR certified. A PolarH10 HR monitor will be worn for the duration of the test. Briefly, treadmill speed will be set at 1.7mph at 0.0% incline for a 4-min warm-up. The protocol begins with speed set at 3.3mph at 0.0% incline for the first minute. Each minute thereafter incline will increase by 1% while the speed is maintained. Rating of perceived exertion (RPE) and overall symptom burden are collected every minute. The test is terminated upon symptom exacerbation, defined as an increase of ≥3 points on a 0–10 visual analogue scale (VAS) [30] or at the point of voluntary exhaustion (9 on a 0–10 Borg-RPE scale [31, 32]). If the participant reaches the maximum incline and is able to continue, speed will be increased by 0.4mph each subsequent minute. Testing will be postponed if the participant has a pre-test overall symptom burden ≥7 on the VAS.

#### Stretching intervention

Participants are asked to complete a 30 min, low-intensity stretching program 5x/week for 6 weeks. A detailed program with each day’s stretches (written and figure format) will be provided. None of the stretches have neck involvement as not to exacerbate neck pain or headache symptoms. All stretches will be demonstrated by a member of the study team at the initial assessment. Participants are instructed to not exceed 50% of age predicted max HR during stretching. HR will be monitored by participants using a PolarH10 HR monitor.

### Measures

The baseline assessment will include participant-reported instruments to collect information on demographics, past medical history, acute rest advice they received following mTBI and self-reported measures of physical and sedentary activity. Outcomes collected at baseline, following 6-weeks and 12-weeks of intervention include symptom burden, assessments of specific symptoms, exercise intolerance and MRI, including spectroscopy, detailed below. A blood draw will also be completed at these time points along with five nights of sleep actigraphy. An electronic follow up (E-FU) will be completed at 3 and 9-weeks post-AEP completion and include specific symptom questionnaires in addition to questions regarding exercise behavior since intervention completion.

### Primary outcome measure

The Rivermead Post-concussion Symptom Questionnaire (RPQ) is a measure of symptom burden which evaluates the severity of 16 commonly experienced post-concussive symptoms [33] frequently used in mTBI and PPCS research. The suggested minimal clinically important difference (MCID) at the time of writing is 4.6pts based on the difference in scores between individuals < 3 months post-mTBI given prolonged rest advice at the time of injury compared to those not given prolonged rest advice (in line with current guidelines) [34].

### Secondary outcome measures

#### Quality of life

Quality of life will be assessed using the Quality of Life After Brain Injury Questionnaire (QOLIBRI). This questionnaire is designed for individuals having suffered a traumatic brain injury and has six subscales containing a total of 37 items [35, 36]. The first four subscales probe satisfaction with health-related quality of life, including cognition, independence and social aspects. The final two subscales address “how bothered” the individual is by emotions and physical problems.

#### Specific symptom severity measures

Symptom questionnaires will be used to assess headache, mood, anxiety, fatigue, dizziness and daytime sleepiness.
*Headache*: The impact of headache on daily function will be assessed with the Headache Impact Test (HIT-6, [37]). The questionnaire’s six items address pain severity, headache impact on activities of daily living, psychological distress and cognitive functioning. Greater total scores are indicative of greater impact with the MCID being a change of 8pts [38].*Mood:* The Patient Health Questionnaire (PHQ-9) will be used to assess the presence and frequency of depressive symptoms [39]. This tool has been validated and is commonly used in individuals with mild to severe TBI [40, 41]. The MCID is 5pts [42].*Anxiety:* The Generalized Anxiety Disorder Scale (GAD-7) is a commonly used measure of anxiety in the mTBI population [43].*Fatigue*: The Fatigue Severity Scale (FSS) is a commonly used brief assessment of fatigue with greater scores indicating more severe fatigue [44].*Dizziness*: The Dizziness Handicap Inventory (DHI) is a 25 item assessment of the handicapping effects imposed by vestibular system disease [45]. Items are grouped into three subscales representing the functional, emotional and physical aspects of dizziness and unsteadiness.*Daytime sleepiness*: The Epworth Sleepiness Scale (ESS) rates the chance of dozing off in 8 different situations [46]. This measure has been widely used in TBI cohorts to assess sleep changes after head injury [47–50].

#### Sleep parameters

Wrist worn actigraphy (MotionWatch 8© [MW8]; CamNTech) will be used to monitor sleep parameters, such as duration and sleep onset latency, pre and post intervention. Sleep diaries will also be collected. It has been suggested that actigraphy assessment is a useful supplement to self-report measures of sleep following TBI [51]. The MW8 has previously been used for sleep analysis in individuals with bipolar disorder [52] and stroke [53]. In older adults, subjective sleep quality has been found to differ from objective measures, such as actigraphy, supporting a best practice of using both measures [54].

#### Exercise intolerance

Exercise intolerance will be measured using the BCTT to assess change in symptom burden (rated on 0–10 VAS) with an increase in HR and exercise intensity. Ability to complete a greater number of stages during the BCTT indicates decreased exercise intolerance and ability to return to play/activity.

#### Blood biomarkers

Blood biomarkers of exercise and recovery will be evaluated to probe underlying mechanisms of response to AEP and SP. Blood samples (7 mL total) will be collected under clean technique from inner elbow at baseline, 6-weeks and 12-weeks of intervention. Markers of overall brain health and response to exercise, specifically brain-derived neurotropic factor, will be analyzed according to validated methods provided by Meso Scale Discovery (SD; Gaithersburd, MD, USA) on their electrochemiluminescence platform. Cytokines will be evaluated to further understand whether there is a chronic inflammatory response to injury in this cohort and whether that is affected by the intervention. Cytokine concentrations will be determined using the Bio-Plex Pro™ Cytokine, Chemokine, and Growth Factor Assays from Bio-Rad (Herkules, CA, USA). Samples will be assayed as instructed by the manufacturer. The plates will be read on a Luminex 200 apparatus (Applied Cytometry Systems, UK). Samples will be acquired and analysed using BioPlex Manager 6.0. Should there be a coefficient of variance of 20% or higher between two replicates, data points will be considered missing. Telomere lengths (TL) will be evaluated as they are known to be neuroprotective and resiliency promoting. In a rodent model, TL has been shown to decrease following mTBI [55]. DNA will be isolated from the red blood cell clot for telomere analysis. TL measurement using qRT-PCR will follow the protocol established by Cawthon [56].

#### Brain imaging outcomes

Magnetic resonance brain imaging will be performed to investigate changes with the AEP and SP to better understand recovery or persistence of symptoms. The imaging protocol includes a T1-weighted structural acquisition, 1H magnetic resonance single voxel magnetic resonance spectroscopy (MRS), arterial spin labeling (ASL) to quantify tissue perfusion, and resting-state functional MRI. The MRS voxels will be in the sensorimotor cortex and the anterior cingulate. Of specific interest are the MRS biomarkers γ-aminobutyric acid (GABA) and glutathione that will be simultaneously measured using a new magnetic resonance spectroscopy method (HERMES, Hadamard Encoding and Reconstruction of MEGA-Edited Spectroscopy) [57]. Glutathione, an antioxidant that combats oxidative stress, is hypothesized to be reduced following brain injury and is expected to change with aerobic exercise. GABA is an inhibitory metabolite which is modulated with brain plasticity. It has been proposed that increased GABA impedes recovery from mTBI [58]. Additional metabolites of interest from MRS (that will be measured using a point-resolved spectroscopy, PRESS) are glutamate, a marker of excitability, and N-acetyl aspartate (NAA), a marker of neuronal health.

